## Description of interventions

Since the whole health facility will receive the intervention or the standard training, it is unrealistic to expect that we could mask the assessors of the practical component. Thus health facilities or instructors will not be blinded to the type of intervention they receive or provide. The health professionals of each health facility will be informed about the training they will receive after the allocation for Standard or MP-ICT training. We will formally assess the theoretical and clinical skills of health care providers through the theoretical and practical exams that all participants in each group will take.

### Standard training

Standard training will be conducted through a theoretical-practical course, which will be administered once during the study period, to all health professionals of the selected facilities, according to the randomization. It is an 8-hour course, with 3 hours of theory (based on suggested readings) and 5 hours of practice, which will take place during a single day, from 9:00 a.m. to 6:00 p.m. The course will be performed by staff of the Neonatal Unit of the National Institute of Child Health, and will be coordinated by an NRP instructor accredited by the American Academy of Pediatrics. Suggested readings will include the following sequential topics: 1) Initial Steps, 2) Positive Pressure Ventilation, 3) Cardiac Massage, 4) Intubation and Medications, and 5) General Review. Practical sessions will be carried out in groups, with 10 or more people per group, and will include all the health professionals of the facility. The practical content part will consist of simulations based on predetermined scenarios using neonatal mannequins and supplies needed for basic and advanced resuscitation, covering each component of the theoretical content. One instructor will be assigned to each group. A baseline and a follow-up theoretical test will be administered.

Participants completing their attendance to theoretical sessions, participating in the simulated practices and approving the printed exams taken the same day will we granted a Standard Certification. The practice will be evaluated qualitatively in terms of assistance, participation and performance of activities.

### Multi-platform ICT training

The continuous process of training and certification in neonatal resuscitation will be developed as a multi-platform format, rechargeable online and accessible offline, and will be complemented with simulated practices. The preliminary format of this system is already in place, and is based on an interactive web platform (
www.rcpneoperu.org), which was initially developed as part of the activities proposed in another project (Project first breath;
http://www.grandchallenges.ca/grantee-stars/0690-01-10, adapted and used with permission). The platforms will contain training packages, and links to review and download neonatal resuscitation tools, technical documents, and regulatory information. During the first three months of the project, the platform will be improved and adjusted to the needs of the fieldwork in Ayacucho and Cusco. The adaptations include increasing hosting, ameliorating usability, uploading packages and videos, improvement of examination and certifications, and tests for readiness. The MP-ICT resource is user-friendly and can be accessed from remote locations through computers, personal portable devices and cell phones. It allows downloading of the different documents, which facilitates learning and theoretical evaluation in an interactive and virtual way, without the presence of instructors or teachers.

Authorized participants will be able to download the information for the theoretical activities in four packages: Package A, B, C and D: each one containing interactive tools as videos and action mazes (as
Quandary), and other videos, documents or short text to read in Spanish. Through the website virtual meetings, as forums or chats, can be initiated. The interactivity is expressed in 360° videos, which allows the user to change the observation point in a recorded environment. The interactivity for action mazes, like Quandary (a software application suite for creating action mazes Version 2.3/Windows;
http://www.halfbakedsoftware.com/quandary.php) has demonstrated that feedback-oriented interactive exercises increase higher-order cognitive skills
^22^. The learning is completed according to the student’s pace and needs, and the platforms offer didactic material. The learning process can be done in groups, but the exam is online and individual, and requires Internet connection. Staff can be trained to become a provider and then qualify to become an instructor. At least one instructor will be certified at each facility in order to train the trainers for continuing education in every facility. Instructors will be given access to the web platform to include news of their activities and to evaluate the practices of aspiring providers in their health facilities. 

The theoretical online exam consists of 40 questions distributed in four modules encompassing basic and advanced neonatal resuscitation. Basic modules include a) Initial Steps of Resuscitation, and b) Positive Pressure Ventilation. Advanced modules include c) External cardiac massage, and d) Intubation and Medications.

Examination for each module allows unlimited attempts, and it is necessary to achieve at least 60% success to be approved. According to approved modules and practices, health personnel can obtain a supplier or instructor certification in both basic neonatal resuscitation and advanced neonatal resuscitation. Two types of examination have been prepared, according to the objective of the applicant. One is an aimed at applicants to Neonatal Resuscitation Provider. The other one, an advanced exam, is for applicants to Neonatal Resuscitation Instructor.

All participants need to complete both the Theoretical and the Practical training components. The platform also will allow the use of an agenda-type tool for scheduling practices for aspiring providers or instructors who have passed their online exam. The Theoretical Component is available after the candidate has been registered in the multi-platform portal, to which they can access through a PC, tablet or cell phone with Internet connection. Access to the content is online the first time, but it may also be offline, after downloading the corresponding training modules.

The Practical Component can be taken only after the Theoretical Component is approved at the participants’ facilities. It consists of face-to-face simulations of predetermined clinical scenarios using mannequins and the needed equipment (bag and mask, suction bulbs, towels, etc). This component has 5 hours of practice, which will take place from 8:00 a.m. to 1:00 p.m. in the morning, or from 2:00 p.m. to 7:00 p.m. in the afternoon. Staff of the Neonatal Unit of the National Institute of Child Health and/or a local trained instructor will guide the practice. An NRP instructor accredited by the American Academy of Pediatrics will coordinate all practices.

Trained instructors will rate the trainees’ performance on the Practical Component, according to assistance and participation in practical activities and qualitative qualification of approving performance. The Practical Component is intended only for health professionals who approved the theoretical exam online and who scheduled their participation with a selected instructor. Practical simulations will be carried out in groups of 3 to 4 people, and an instructor will be assigned for each group. They do not require theoretical presentations, pre-test or post-tests.

To be granted an MP-ICT Certification the trainee needs to have passed the online theoretical exam and the practical skills assessment.

An example of MP-ICT training can be found in
Supplementary File 2.

### Outcomes

Our primary outcome is the percentage of infants with heart rate equal or greater than 100 per minute at two minutes of life. This outcome is an adequate proxy for effective response to neonatal resuscitation measures in the delivery room
^20,
21,
23^.

The secondary outcomes are described in our secondary objectives.

### Randomization

Computer-generated random numbers will be used to assign the selected health facilities to either MP-ICT training (Intervention Group) or to standard training (Control Group). There will be a matching process of health facilities by proportion of groups of non-medical professionals (nurses and obstetricians) and by availability of basic equipment and maternal and newborn care supplies (the information for which will be available to the health regional directorates), to ensure that health facilities are comparable. Once paired, they will be randomly allocated through a blocked randomization, to ensure a balanced distribution of facilities in each group.

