## Introduction

### Background

Approximately 10% of newborns may have difficulty breathing at birth and require urgent support from trained personnel
^1^. The first 60 seconds of life in those conditions require immediate and effective interventions to help infants survive
^2^. Unfortunately, some newborns in low- and middle-income countries do not have access to appropriately trained personnel, making asphyxia one of the leading causes of neonatal death in those settings
^3^.

In Peru, about 550,000 births occur per year (Peruvian Institute for Statistics and Informatics 2015;
https://www.inei.gob.pe), and this means that approximately 6 newborns each hour may require respiratory support at birth. Problems in training health workers for adequate support of newborns is aggravated by a high turnover rate of personnel, particularly in small cities and rural areas, which hampers regular conduction of local training programs, even if they are perceived as a positive incentive
^4^. Peru is a high-middle-income country that has made significant progress in reducing neonatal and infant mortality in the last decade, despite inequities in access to health services, especially in rural areas of the Amazon and the Andes
^5,
6^. In the years 2011–2012, the Peruvian neonatal mortality rate was estimated at 12.8 per thousand live births
^7^, with an estimated 20 per thousand live births for Pasco and Cusco regions, 15 for Ayacucho and Amazonas, 12 for Huancavelica and 8 for Lima
^8^. From 2000 to 2013, neonatal mortality in Peru fell by 51% from 16.2 deaths per 1000 livebirths to 8.0
^9^.

The Neonatal Resuscitation Program (NRP) from the American Academy of Pediatrics, includes evidence-based clinical guidelines and was designed to train health care providers and instructors in hospital settings. The NRP is a paid course that has 2 components, an online component (internet-dependent) and a practice/evaluation component
^1,
10^. A variant of the NRP program is the Helping Babies Breath (HBB) program, which was designed to provide neonatal resuscitation training in resource-poor settings. The HBB has shown to reduce neonatal mortality and it is proposed as a successful global intervention
^11^. However, the greatest limitation of these programs is the need for recurrent training with a frequency of less than 12 months to maintain the acquired skills and knowledge
^12^.

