### Inclusion and exclusion criteria

Primary and secondary level facilities located in Ayacucho and Cusco that have a neonatal mortality rate higher than 15 per 1,000 livebirths will be eligible. Health facilities whose authorities refuse participation of their health professionals, facilities with less than 290 births a year, facilities located at more than 210 kilometers from the department capital, and those located in high-risk areas due to social unrest will be excluded. Health professionals who attend deliveries and accept their voluntary participation will be included after signing informed consent forms.

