### Sample size

We must emphasize that our study will be conducted at a pilot scale and thus we considered the minimum sample size for such study level. Assuming the occurrence of about 4,000 births during a period of 6 months of filed study observation, we aim at discriminating a 4% difference in the proportion of newborns with heart rate equal or greater than 100 beats per minute at two minutes of life between the intervention and the control group
^18^. We would require 12 clusters (health facilities) divided in two arms, with six facilities allocated to each arm, and with an average of 334 deliveries per facility during the observation period. The proposed power of the study is 80% and the acceptable alpha error is 5%. The percentage for heart rate >100 bpm at two minutes of life during suitable resuscitation using self-inflated bag is 90%
^21^, and it is the expected value for the intervention group. For the control group, at least 4 percentage points below the value achieved in the intervention group is expected (i.e. no more than 86%).

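### Facilities are paired on staff mix, equipment and supplies but not on level of care or department; pairing within level first is a cheap way to remove avoidable variance, provided the analysis then uses the pairs.

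*Protocol article*

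**What the plan says.** The protocol article (Randomization) sets out a "matching process of health facilities by proportion of groups of non-medical professionals (nurses and obstetricians) and by availability of basic equipment", and extends the list to maternal and newborn care supplies. The stated aim is comparability of the facilities. The pairs are then allocated by blocked randomization.

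Eligibility is wider than these factors. The Inclusion and exclusion criteria open with "Primary and secondary level facilities located in Ayacucho and Cusco", so level of care and department both vary. The Background reports regional neonatal mortality "with an estimated 20 per thousand live births for Pasco and Cusco regions, 15 for Ayacucho and Amazonas".

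The primary outcome (Outcomes) is the percentage of infants with a heart rate of at least 100 at two minutes, with no restriction to resuscitated infants. The sample size likewise counts all births: 12 facilities, "with six facilities allocated to each arm, and with an average of 334 deliveries per facility during the observation period", to separate 90% from 86%.

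The named baseline assessment (Effectiveness assessment) covers equipment and supplies. The stated primary test (Statistical analysis) is chi-square or Fisher, with no term for pair, level or department.

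**The concern.** A percentage over all births depends on how many newborns are depressed at birth as well as on how well they are resuscitated. Staff mix, equipment and supplies describe the provider side. None measures patient risk. If higher-risk births tend to go to secondary-level facilities (an assumption; the documents do not say so), level of care is a natural source of outcome differences between facilities.

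With six facilities per arm, randomization alone cannot be relied on to balance such a factor. Pairing is the only protection the protocol states, because neither the baseline assessment nor the analysis corrects an imbalance afterwards. At stake is the precision of the treatment comparison and, under the stated unadjusted test, the false-positive rate.

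**Working it through.** **The plan's own figure.** For 86% v 90%, two-sided alpha 5% (sidedness not stated) and 80% power, the usual two-proportion formula gives 1,035 births per arm. The plan has 6 x 334 = 2,004 per arm. The ratio 2,004/1,035 = 1.94 is an unstated design effect, which implies an ICC of (1.94 - 1)/(334 - 1) = 0.0028. The stated 80% is reproduced only with that ICC.

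**Assumed inputs.** The number of secondary facilities and the outcome gap by level are not in the documents. I take 4 of 12 secondary, a gap d of 3, 6 or 9 points, and no credit for the present matching factors.

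**Chance of imbalance.** A hypergeometric split of 4 secondary facilities over 6 + 6 gives 2-2 in 45.5%, 3-1 in 48.5% and 4-0 in 6.1%. With 2 of 12 secondary, both fall in one arm with probability 45.5%.

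**Shift of the arm difference.** A 3-1 split moves it by d x (3 - 1)/6 = d/3, that is 1, 2 or 3 points. A 4-0 split moves it by 2d/3, that is 2, 4 or 6 points.

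**Standard deviation of the arm difference.**
- Sampling only: sqrt[(0.9 x 0.1 + 0.86 x 0.14)/2,004] = 0.01025, or 1.0 point.
- Between-facility variance from level: d^2 x (1/3)(2/3) x 12/11. It enters the arm difference as 2/6 of that value.
- Totals: d = 3, sqrt(0.01025^2 + 0.0085^2) = 1.3 points; d = 6, sqrt(0.01025^2 + 0.0171^2) = 2.0 points; d = 9, sqrt(0.01025^2 + 0.0256^2) = 2.8 points.
- If all pairs are concordant on level, the level term is zero and the total returns to about 1.0 point.

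**False-positive rate of the stated chi-square test.** The null standard error is sqrt(2 x 0.88 x 0.12/2,004) = 1.03 points, so an observed difference of about 2.0 points is significant. Weight the rejection rate by the split probabilities, with no other between-facility variation:
- d = 3: 0.455 x 0.05 + 0.485 x 0.164 + 0.061 x 0.495 = about 13%.
- d = 6: 0.455 x 0.05 + 0.485 x 0.495 + 0.061 x 0.974 = about 32%.
- d = 9: 0.455 x 0.05 + 0.485 x 0.832 + 0.061 x 1.0 = about 49%.
- With all pairs concordant on level: about 5%.

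**Power by pairing and analysis.** Simulation under the same assumptions, 90% v 86%, facility-level tests:

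| Pairing on level | Test | d = 3 | d = 6 | d = 9 |
|---|---|---|---|---|
| No | unpaired t, 10 df | 77% | about 40% | 24% |
| Yes | unpaired t, 10 df | 81% | about 33% | 3% |
| Yes | paired t, 5 df | 87% | about 87% | about 88% |

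Same-level pairs with an unpaired test lose power at the larger gaps. The level variance stays in the denominator although it has left the numerator.

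**Are the assumed gaps consistent with the plan?** Dividing the level variance by 0.88 x 0.12 = 0.1056 gives the ICC that level alone would produce: 0.0021, 0.0083 and 0.019 for gaps of 3, 6 and 9 points. Only the 3-point gap fits within the 0.0028 implied by the sample size.

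**The case against.** The investigators already pair and block-randomize, in what they call a pilot-scale study. Their factors bear directly on resuscitation, and staff mix, equipment and supplies plausibly track level. The figures above give them no credit, so on average they overstate the problem. The exception is an unlucky pairing: if each of four secondary facilities were matched with a primary one, the level component at a 6-point gap would be sqrt(4)/6 x 6 = 2.0 points rather than 1.7. Every magnitude rests on assumed inputs. All of this stands, and it limits the size of the point.

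Three stronger readings are tempting and are not supported.
- A reader might infer that the arms can easily differ by the whole effect sought. A 4-point shift needs a 4-0 split (6.1%) with a gap of at least 6 points, or a 3-1 split with a 12-point gap. At the ICC implied by the sample size, true facility differences alone would separate the arms by 4 points with probability below 0.1%. It becomes 3.3% at an ICC of 0.01 and 13% at 0.02.
- A reader might infer bias. Allocation is random, so the imbalance is variance. The harm comes from an analysis that ignores it.
- A reader might infer that better pairing raises power whatever the analysis. The middle row of the power table shows otherwise.

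The departmental contrast is also weak evidence. Mortality of 20 v 15 per 1,000 is a regional estimate for 2011-2012, a gap of 0.5 percentage points, and says nothing about heart rate at two minutes. Nor can facility mortality be assumed to be in hand: the Abstract applies the threshold to provinces and Settings to regions. At 290 births and 15 per 1,000 it would be about 4 deaths a year (290 x 0.015 = 4.35), too few to order pairs.

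Finally, two levels by two departments makes four strata for six pairs. If all four are odd in size, two mixed pairs are unavoidable, so strict pairing on both factors is too tight.

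**Conclusion.** The point holds as a cheap improvement. The matching list omits level of care and department, both vary among eligible facilities, both are known beforehand, and no later step named in the article corrects an imbalance. If 4 of 12 facilities are secondary and differ by 3 to 9 points, leaving level to chance raises the standard deviation of the arm difference from about 1.0 to 1.3-2.8 points. The lower end is the one compatible with the protocol's implied ICC. The range is roughly an upper bound to the extent that the present factors track level. The documents supply neither the gap nor the number of secondary facilities, so the actual size is unknown. The case rests on the low cost of the remedy, not on a demonstrated imbalance.

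**What to change.** In Randomization, form pairs within the same level of care first, and within the same department where a partner exists. Then choose among the remaining candidates on staff mix, equipment and supplies. Annual births, needed anyway for the 290-birth exclusion, may break ties. Do not order on facility neonatal mortality. Allow mixed pairs where numbers are odd: pairing on level first leaves at most one pair mixed on level, which shifts the arm difference by d/6, or 0.5, 1.0 or 1.5 points for the gaps above.

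In Statistical analysis, keep the pairs (or level) in a facility-level comparison, since the power gain is realised only then.

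Table 1 places allocation before August 2017. If it has been done, tabulate level and department by arm and adjust for level in the facility-level analysis.

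No facilities or births are added. The cost is looser matching on staff mix, equipment and supplies, which with only six pairs may be noticeable, or one degree of freedom if level is handled by adjustment.

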### Study design

The proposed study design is a randomized cluster trial. The units of study and analysis will be twelve health facilities from Ayacucho and Cusco departments. Each health facility will be a cluster. Clusters will be randomly assigned either to the MP-ICT course and certification package (intervention) or to the standard training and certification package (control). Additional details are shown in
Table 1.

**Table 1. T1:** Schedule of enrolment, interventions, assessments and final report: RCPNEOPERU Project.

	STUDY PERIOD									
	Project Management		Allocation	Post-allocation		Pause	Assessments			Close-out
BIMESTER	*B _-2_*	*B _-1_*	*0*	*B _3_*	*B _4_*	*B _5_*	*B _6_*	*B _7_*	*B _8_*	*B _9_*
	*2017-04* *2017-05*	*2017-06* *2017-07*		*2017-08* *2017-09*	*2017-10* *2017-11*	*2017-12* *2018-01*	*2018-02* *2018-03*	*2018-04* *2018-05*	*2018-06* *2018-07*	*2018-08* *2018-09*

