### Statistical analysis

An intention to treat analysis will be performed, including all clusters as they were initially assigned, including premature withdrawals. Additionally, a per-protocol analysis will be carried out, where only clusters that have completed the study protocol will be considered. The primary outcome will be compared in each arm using Chi-square test if the variable of distribution is normal, or alternatively through the Fisher’s exact test. Secondary outcomes will be compared using the Student’s t-test or the Kruskal-Wallis test. For supplementary oxygen use, the Chi-square test or Fisher’s exact test will be used.

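### Facilities are paired before allocation, but the named tests use neither the pair nor, for a chi-square on infants, the facility; the primary analysis should work on the six within-pair differences.

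*Protocol article*

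**What the plan says.** The Randomization section of the protocol article describes matching facilities on the share of nursing and obstetric staff and on basic equipment and supplies. It continues: "Once paired, they will be randomly allocated through a blocked randomization, to ensure a balanced distribution of facilities in each group". The Sample size section fixes the numbers: "We would require 12 clusters (health facilities) divided in two arms, with six facilities allocated to each arm", "with an average of 334 deliveries per facility during the observation period". The Study design section declares the facility to be the analysis unit: "The units of study and analysis will be twelve health facilities from Ayacucho and Cusco departments".

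The Statistical analysis section then says: "The primary outcome will be compared in each arm using Chi-square test if the variable of distribution is normal", with Fisher's exact test as the alternative. For the rest: "Secondary outcomes will be compared using the Student’s t-test or the Kruskal-Wallis test", with chi-square or Fisher again for supplementary oxygen. No sentence in the article brings the pairs into any comparison.

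**The concern.** Restricting the randomisation to matched pairs changes the sampling variance of the treatment difference, so the analysis has to reflect it. Here two layers of the design drop out of the named tests. A chi-square on infants treats about 4,000 births as independent, although whole facilities were allocated. An obvious repair, comparing six facility proportions with six others, restores the facility but still ignores the pair.

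The two omissions err in opposite directions. Ignoring the facility makes intervals too narrow and produces false positives. Ignoring only the pair makes intervals too wide when matching works, and discards precision that a trial with twelve clusters can hardly spare. The result is meant to support national scale-up, so both matter.

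**Working it through.** **The plan's own figures.** 12 × 334 = 4,008, which agrees with about 4,000 births. For 90% against 86%, two-sided 5% and 80% power with independent births, the number per arm is [1.96·√(2·0.88·0.12) + 0.8416·√(0.9·0.1 + 0.86·0.14)]² / 0.04² = 1,035. The planned 6 × 334 = 2,004 per arm would give 97.4% power. The stated 80% therefore implies an unstated design effect of 2,004/1,035 = 1.94, that is, an ICC of (1.94 − 1)/333 ≈ 0.0028 (0.0025 with continuity correction). The article gives no ICC and no matching correlation. I use ICC 0.003 (close to the implied value) and 0.01, with ρ, the correlation of true rates within a pair, at 0 and 0.5. All four values are assumptions.

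**Standard errors of the difference.** Take the mean proportion 0.88, so v = 0.88 × 0.12 = 0.1056. The between-facility variance is b = ICC·v and the within-facility variance is w = (1 − ICC)·v/334. At ICC 0.01, b = 0.001056 and w = 0.000313.
- Pooled infants (chi-square): √(2v/2,004) = 0.0103.
- Unpaired facility analysis: √(2(b + w)/6) = 0.0214.
- True value under pairing, ρ = 0.5: √(2(b(1 − ρ) + w)/6) = 0.0167.

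**Size of the chi-square on infants.** This is 2Φ(−1.96 × 0.0103/0.0167) ≈ 23%. At ICC 0.003 the true standard error is 0.0126, and the size is 2Φ(−1.96 × 0.0103/0.0126) ≈ 11%.

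**Simulation of six pairs of facilities, 334 births each** (size at 88% in both arms; power at 90% against 86%):

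| ICC | ρ | Size: chi-square on infants | Size: unpaired t, 10 df | Size: paired t, 5 df | Power: unpaired t | Power: paired t |
|---|---|---|---|---|---|---|
| 0.003 | 0 | 17% | 5% | 5% | 70% | 60% |
| 0.003 | 0.5 | 11% | 2.8% | 5% | 72% | 72% |
| 0.01 | 0 | 35% | 5% | 5% | 39% | 33% |
| 0.01 | 0.5 | 23% | 1.9% | 5% | 38% | 49% |

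**Interval width at ICC 0.01, ρ = 0.5.** The half-widths are ±1.96 × 0.0103 = ±2.0 points pooled, ±2.228 × 0.0214 = ±4.8 points unpaired and ±2.571 × 0.0167 = ±4.3 points paired. The unpaired interval is thus about 11% wider than the paired one on true standard errors. Averaged over simulated trials it is about 13% wider. The ratio of standard errors alone, 0.0214/0.0167 = 1.28, overstates the gain because the paired interval carries the larger critical value.

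**When pairing pays.** With six pairs, the paired t-test has more power than the unpaired one once the within-pair correlation of observed facility proportions exceeds about 0.20 to 0.22. At ICC 0.01 and ρ = 0.5 that correlation is bρ/(b + w) = 0.000528/0.001369 = 0.39.

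**Two alternatives.** Stratifying infants by pair with a Mantel-Haenszel test does not help: its size is 20.3% against 20.2% for the plain chi-square at ICC 0.01, ρ = 0.6. The exact sign-flip test has 2⁶ = 64 allocations. Its smallest two-sided p-values are 2/64 = 0.031 and 4/64 = 0.0625, so it rejects only when all six pairs favour the same arm. Its power at ICC 0.01 and ρ = 0.5 is about 32%.

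**The case against.** A reader might infer that, because the pairs are ignored, the planned primary test is conservative and its intervals too wide. The document does not support that. It names a chi-square or Fisher test, and on infants this errs the other way. The conservative behaviour arises only after someone repairs the clustering with an unpaired facility-level test. Equally, the document does not show that the stated 80% power is false, only that it does not follow from the stated inputs.

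Other objections stand in part:
- That the block is the pair is inferred. It is the natural reading, but the article should say so.
- The gain from pairing rests on assumed values. Near the ICC implied by the plan's own power, with ρ = 0.5, paired and unpaired power are equal at 72%. A pre-specified unpaired facility-level analysis would therefore be defensible, though conservative if matching works.
- The article condenses a fuller protocol, and an analysis plan may exist. Detail left to those would be no fault. Here, however, the article commits to particular tests that do not fit its own design.
- One might argue that the per-protocol analysis ("Additionally, a per-protocol analysis will be carried out, where only clusters that have completed the study protocol will be considered") undoes the matching, since losing one facility leaves its partner unmatched. That is minor. Intention to treat keeps all clusters, the per-protocol analysis is additional, and dropping whole pairs would discard compliant facilities from only twelve.

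**Conclusion.** The mismatch between allocation and analysis is real and visible in the text. The larger part of the harm comes from ignoring the facility: type I error of about 11% at ICC 0.003 and about 23% at ICC 0.01, both with within-pair correlation 0.5. The part specific to pairing is smaller and conditional. At ICC 0.01 and the same correlation, an unpaired facility-level repair has size of about 1.9% and 11 points less power than the paired test. At ICC 0.003 the power difference vanishes. These figures assume pair-wise allocation, equal facilities of 334 births, a two-sided 5% test, and ICC and matching values that the article does not give. The paired facility-level t-test held close to 5% in every setting examined.

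**What to change.** State that allocation is within pairs, one facility to each arm. Make the primary analysis a paired t-test on 5 df of the six within-pair differences in facility proportions. The alternative is a mixed model that contains both facility and pair, with a small-sample correction. Say explicitly that stratifying infants by pair is not sufficient. An exact sign-flip test can be listed as a sensitivity analysis, but not as the primary test. Use the same pairing for secondary outcomes. A rule for broken pairs in the per-protocol analysis is optional.

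The change is to wording only, needs no new data, and should be made before outcomes are seen so that the choice between paired and unpaired is not driven by the results. The price is 5 rather than 10 degrees of freedom. If the matching factors turn out unrelated to outcome, power falls from 39% to 33% at ICC 0.01 and from 70% to 60% at ICC 0.003.
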